## Abstract

Major depressive disorder (MDD) is the most common psychiatric disease worldwide with a huge socio-economic impact. Pharmacotherapy represents the most common option among the first-line treatment choice; however, only about one third of patients respond to the first trial and about 30% are classified as treatment-resistant depression (TRD). TRD is associated with specific clinical features and genetic/gene expression signatures. To date, single sets of markers have shown limited power in response prediction. Here we describe the methodology of the PROMPT project that aims at the development of a precision medicine algorithm that would help early detection of non-responder patients, who might be more prone to later develop TRD. To address this, the project will be organized in 2 phases. Phase 1 will involve 300 patients with MDD already recruited, comprising 150 TRD and 150 responders, considered as extremes phenotypes of response. A deep clinical stratification will be performed for all patients; moreover, a genomic, transcriptomic and miRNomic profiling will be conducted. The data generated will be exploited to develop an innovative algorithm integrating clinical, omics and sex-related data, in order to predict treatment response and TRD development. In phase 2, a new naturalistic cohort of 300 MDD patients will be recruited to assess, under real-world conditions, the capability of the algorithm to correctly predict the treatment outcomes. Moreover, in this phase we will investigate shared decision making (SDM) in the context of pharmacogenetic testing and evaluate various needs and perspectives of different stakeholders toward the use of predictive tools for MDD treatment to foster active participation and patients’ empowerment. This project represents a proof-of-concept study. The obtained results will provide information about the feasibility and usefulness of the proposed approach, with the perspective of designing future clinical trials in which algorithms could be tested as a predictive tool to drive decision making by clinicians, enabling a better prevention and management of MDD resistance.

## Introduction

1

The World Health Organization (WHO) declared that “there is no health without mental health.” Mental health is a state of well-being in which an individual is aware of his or her own abilities, can cope with the normal stress of life, can work productively and is able to contribute to his or her community. Major depressive disorder (MDD) is the most common psychiatric disease worldwide and represents a leading cause of years lived with disability. In turn, this leads to an enormous socio-economic impact. Indeed, MDD represents the costliest psychiatric disorder in Europe (1). Moreover, it has been largely demonstrated that women are nearly twice as likely as men to be diagnosed with MDD. Different biological and environmental factors seem to increase the risk of depression in women; however, this issue remains largely unknown (2).

The main goal of treating MDD is to achieve remission and to maintain the therapeutic effects over time. Despite the availability of different classes of antidepressant drugs, the success of pharmacological treatment is still unsatisfactory, and matching a patient to his/her optimal treatment generally requires multiple trials of different treatments administered adequately in terms of doses and timing, with the sobering observation that the more treatments tried without success, the less likely a successful outcome. Only about 30 and 40% of patients experience remission after the first and second treatment course, respectively, and up to one third of them are classified as resistant to treatment (Treatment-Resistant Depression, TRD) (3, 4). This causes suffering for patients and their families and significantly contributes to pushing up costs for healthcare services.

The observation that TRD occurs despite the high variety of pharmacological drugs acting through different mechanisms of action suggests a possible common mechanism in resistant depression. This is consistent with evidence from studies that combine pharmacology, genetics, and brain imaging data, showing that non-response to a wide range of treatments share common etiology and common neuronal mechanisms that still need to be investigated (5).

Several clinical variables are associated with an unfavorable treatment outcome in MDD, such as earlier disease onset, greater severity, presence of psychiatric comorbidity, suicidal behaviors, and early life adversity (6). From a biological perspective, TRD is associated with specific molecular underpinnings, which are only partly known. Concerning transcriptomics, there is evidence of distinct patterns of gene expression, both in the central nervous system and in peripheral tissues, such as blood (7). Moreover, expression alterations of both coding genes and microRNAs (small non-coding RNAs that regulate gene expression) have been related to the lack of response to antidepressant treatment (8). In addition, several studies also indicated the existence of a genetic vulnerability to non-response to antidepressant drugs and TRD (7, 9). In animal models, RNA-seq on different brain regions after antidepressant treatments showed largely distinct gene changes associated with treatment response (10). Moreover, accumulating evidence shows that transcriptional changes seen across several brain regions in animal models of depression coincide with genetic risk factors in depressed human patients. This indicates the likelihood that peripheral changes in gene expression might reflect to some extent some aspects of brain function (11).

In this context, the identification of predictive markers will help the early detection of non-responder patients, who may be more prone to later develop TRD. However, the use of single sets of markers (either clinical or molecular) have shown limited predictive power and low replicability, indicating that the etiology of MDD in non-responder patients remains to be better understood. Through multi-omics integration, machine learning methods have the potential to model the interactions between several molecular layers (such as DNA or RNA) to predict a clinical endpoint using a holistic model (12). It is conceivable that the integration of diverse sets of predictors might increase the accuracy in the identification of non-responder and TRD patients.

The overall objective of the PROMPT (“Toward PrecisiOn Medicine for the Prediction of Treatment response in major depressive disorder through stratification of combined clinical and -omics signatures”) consortium, which is funded by the European ERA PerMed funding scheme, is to apply an integrated precision medicine approach in MDD through the combination of clinical, genomic, transcriptomic and sex-related data. The core objective is to create a new algorithm for the prediction of treatment response, which could be tested and validated in future clinical trials. This algorithm might represent a new tool for clinicians to drive decision-making, based not only on patients’ clinical features, but also on their genetic and transcriptomic background. An additional objective is to evaluate the potential use of a predictive pharmacogenetic tool in clinical practice from different perspectives and needs of various stakeholders involved in MDD treatment. Moreover, it is important to stress that the development of such an innovative precision medicine tool is central, but only part of the process to advance MDD treatment. Considering the later clinical application is crucial, and shared decision making (SDM) is increasingly viewed as the gold standard in patient-healthcare professional communication (13). SDM is a patient-centered approach that aids empowerment by supporting patients to actively take part in developing an informed decision about further treatment jointly with healthcare professionals based on clinical options as well as a patient’s individual preferences (14–16). Although SDM has been reported to lead to better decisions, increased patient participation, patient satisfaction, and treatment adherence and avoidance of overtreatment, its application in the mental health field is still rare (16, 17). Furthermore, multiple factors have been reported to influence SDM. This includes personal characteristics of the engaging parties, such as sex, age, clinical knowledge, years of experience, spoken language, or the level of education, factors relating to the interaction process, such as providing information or establishing a trustful relationship, and factors concerning broader structures of the healthcare system, for example, time constraints (18). In PROMPT, we consider application and SDM from the beginning and seek to identify factors that might come into play when patients and healthcare professionals come together to decide specifically about using the developed algorithm in clinical practice.

## Methodology

2

### Study design

2.1

The overall methodology of the project is based on a two-phase design (Figure 1). In the first phase (training phase, retrospective design), 300 already recruited MDD patients, including 150 TRD and 150 responders considered as extremes phenotypes of response, will undergo a deep clinical and omics profiling. These data will be exploited to develop an innovative integrative algorithm for the prediction of MDD treatment outcome.

**Figure 1 fig1:**
[figure not shown]
Study design phases of PROMPT project.

In the second phase (testing phase, prospective observational design), a new naturalistic cohort of 300 MDD patients will be recruited, and omics profiled to assess the predictive reliability of the algorithm under real-world conditions. Furthermore, in the second phase of the project, surveys involving the general population, patients as well as health care professionals, integrated with focus groups, will be performed on the topic of personalized, tool-assisted, and shared decision making processes. This will permit soundly to take into account the patients’ perspective, their needs on the use of predictive tools for MDD treatment and will support the process of patient empowerment in Personalized Psychiatry.

### Phase 1: training phase

2.2

In this first project phase, two groups of clinically well-characterized MDD patients (TRD and responders), already recruited in the context of ongoing projects, will be selected considering them as extreme phenotypes of response allowing to train models on a dichotomous outcome. All patients will be profiled with genomic, pharmacogenetic, transcriptomic and miRNomic high-throughput technologies to create an integrative machine learning (ML) algorithm discriminating between the two groups.

#### Study participants and clinical assessment

2.2.1

Three hundred MDD patients were already recruited from one unit participating in PROMPT consortium (IRCCS Fatebenefratelli, Brescia, Italy): half were classified as TRD and the other 150 as responders. For all of them, diagnosis of moderate to severe MDD according to the DSM-IV was confirmed using the Italian version of the SCID-I diagnostic scale. The diagnosis of personality disorders was made on the basis of clinical symptoms evaluation in agreement with the DSM-IV. Exclusion criteria were the following: (a) a lifetime history of schizophrenic, schizoaffective, or bipolar disorder; (b) personality disorder, substance abuse, alcohol abuse or dependency, obsessive compulsive disorder (OCD), or post-traumatic stress disorder (PTSD) as the primary diagnosis; (c) comorbidity with an eating disorders; (d) comorbidity with alcohol and substance dependence; (e) intellectual disability and cognitive impairment; (f) neurological disorders (i.e., Parkinson’s disease, multiple sclerosis, Alzheimer’s and other dementias, epilepsy, strokes, brain tumors, traumatic conditions of the nervous system); (g) comorbidity with other severe medical illness and severe autoimmune diseases (i.e., cancers, Crohn’s Disease, Rheumatoid Arthritis (RA), Lupus, Scleroderma, Psoriasis, Myasthenia gravis, Sjögren syndrome, Systemic lupus erythematosus); (h) pregnancy.

On the basis of clinical evaluation, TRD was defined as a failure of treatment to produce response or remission for patients after two or more treatment attempts of adequate and recommended dose and duration. Based on clinical judgment by the treating psychiatrists, MDD patients were classified as responders when they achieved response or remission in terms of a reduction in symptomatology with the first antidepressant treatment attempt of adequate dose and duration. For all patients, detailed socio-demographic (such as, age, sex, working and marital status) and clinical information (such as, age of onset, severity, psychiatric and physical comorbidities) was collected. Symptom evaluations were made using Montgomery-Åsberg Depression Rating Scale (MADRS) at the presentation of the patients to psychiatric services or hospital, in concomitance with the blood collection.

#### Omics profiling

2.2.2

DNA and RNA extracted from peripheral blood samples are prepared for genomic, pharmacogenetic, transcriptomic and miRNomic profiling. DNA is extracted from whole blood samples using the Gentra Puregene Blood kit (Qiagen), according to the manufacturer’s instructions. Total RNA is extracted from blood already collected in PAXGene tubes and stored at −80°C with the PAXGene Blood miRNA Kit (Qiagen), designed for the simultaneous isolation of small and large RNAs. RNA is quantified and quality-checked through the Agilent 2,100 Bioanalyzer system and aliquots are sent to the involved project partners for transcriptomic and miRNomic profiling.

#### Genomic and pharmacogenetic profiling

2.2.3

All the patients are genotyped through the GWAS array Infinium PsychArray-24 v1.3 BeadChip. In addition, all of them are genotyped with customized TaqMan OpenArray plates on a QuantStudio 12 K Flex Real-Time PCR System (Applied Biosystems, Foster City, California, United States) to obtain pharmacogenomics profile that include the following single-nucleotide polymorphisms (SNPs) in relative genes (15 in *CYP2D6*, 10 in *CYP2C19*, 4 in *CYP2B6*, 2 in *CYP2C9*, 8 in *CYP1A2*, 8 in *CYP3A4*, 11 in *ABCB1*). We also genotype the 5-HTTLPR (short/long allele) and rs25531 polymorphisms (A/G genotype) in the *SLC6A4* gene.

#### Transcriptomic profiling

2.2.4

Abundant RNAs such as ribosomal and beta globin transcripts are removed starting from 10 ng total RNA using the Illumina Stranded total RNA Prep with Ribo-Zero Plus kit. RNA library preparation is performed following manufacturer’s recommendations. Final samples pooled library preparations are sequenced on a Novaseq 6,000 ILLUMINA, at a depth of 2x30Millions of 100bases reads per sample after demultiplexing (19).

#### MiRNomic (+ other small RNA) profiling

2.2.5

MiRNomic (+ other small RNA) profiling is conducted by small RNA-Seq. The NEBNext^®^ Small RNA Library Prep Set for Illumina® kit is used with minor modifications. Adaptor ligation, first strand cDNA synthesis, and PCR enrichment are performed. Library amplification utilizes custom Unique Dual Indexes (UDIs). Purification steps involve AgenCourt AMPure XP beads, and library analysis is done using Agilent Bioanalyzer. Size selection is performed using 6% Novex TBE PAGE Gels, and quantification is carried out with the KAPA Library Quantification Kit. Sequencing yields 20–30 million single-end 50 bp reads per sample on a NextSeq2000 (Illumina).

#### Bioinformatic analysis

2.2.6

Quality assessment is done with FastQC, and reads are trimmed using Cutadapt before mapping. For miRNOmic data, sequences with length < 16 nucleotides are discarded. Reads are aligned to the reference genome (hg38 and miRBase v22 for RNASeq and miRNOmic, respectively) with STAR. Counts table is generated using featureCounts, filtered for lowly expressed genes, and analyzed using linear models (limma) for differential expression analysis. Functional analysis utilizes available annotations in functional genomics resources. Network-based approaches are employed to visualize miRNA-target connections and perform gene ontology (GO) analyses. STRINGdb is used for protein–protein interaction retrieval, igraph for network analysis, and clusterProfiler for GO and pathway enrichment analyses. Differential expression of miRNAs is validated by qPCR.

#### Sample size calculations

2.2.7

Power analyses were assessed using Bioconductor R packages ssizeRNA (20), ssize.fdr (21) and ssize (22). Parameters were obtained from seven publications of expression data in MDD patients (23–29). In cases where adjusted *p*-values were not reported, we adjusted them using the function p.adjust, with the FDR method. Dispersion of genes was not specified in the seven publications so we considered a 0.3 for all of them. Assessed experiments vary considerably in conditions, methods and results, which resulted in sample size estimations per group ranging between 11 and 121. Hence, we aim at a sample size of 150 per group, which exceeds the largest sample size calculated because we want to be conservative for the multi-omic nature of the study, but is also realistic considering our recruitment capacity.

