#### Integration of clinical and − omics data

2.2.8

With the purpose of understanding the molecular mechanisms of TR and identifying potential biomarkers to be used as features in a predictive model of treatment response (TR), we use multi-staged strategies such as differential gene/miRNA expression (limma), knowledge-driven miRNA-target analysis and Weighted Gene Co-expression Network Analysis (WGCNA), as explained previously. Nonetheless, given that we have three different omics layers (DNA, RNA miRNA), we also take advantage of meta-dimensional methodologies, which involve analyzing all omics layers simultaneously. These methodologies are especially powerful to capture complex interactions between the individual molecular layers and possibly identify new integrated molecular features (reduced dimensionality) that explain the phenotype. These new features are then being assessed, as features for a predictive model. We will employ different methods including iClusterPlus, which uses penalized likelihood approach with lasso penalty to associate a genomic feature with a phenotype, multi-omics factor analysis (MOFA), which infers an interpretable low-dimensional data representation as hidden factors or the partial least squares discriminant analysis (PLS-DA), implemented in mixOmics, which has increasingly been used in omics research as a supervised version of PCA that preserves in its first PC as much covariance as possible between the original data and its labeling (30). To avoid overfitting of the algorithm, this discovery analysis is done on two thirds of the Phase 1 data, keeping one third unseen from any training process.

Importantly, given the high relevance of the sex dimension in TR, we will stratify all analyses according to sex. This might as well help to further decipher the influence of sex on TRD. We also clinically assessed anxiety disorders in comorbidity, more frequently present in women, and will be analyzed with respect to omics data and putative sex effect.

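### The Phase 1 margin of 150 over 121 per group holds for the recruited total, not for the discovery analysis, which uses about 100 per group

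*Protocol article*

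**What the plan says.** Section 2.2.7 (Sample size calculations, Phase 1) uses three packages for sizing expression experiments, with parameters from seven published studies of expression in MDD and an assumed gene dispersion of 0.3. It reports "sample size estimations per group ranging between 11 and 121". It then concludes "we aim at a sample size of 150 per group, which exceeds the largest sample size calculated", and gives as the reason "because we want to be conservative for the multi-omic nature of the study". It mentions neither a hold-out nor a split by sex.

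Section 2.2.8 (Integration of clinical and -omics data) describes feature discovery: differential expression with limma, miRNA-target analysis, co-expression networks and the integrative multi-omics methods. It states that "this discovery analysis is done on two thirds of the Phase 1 data, keeping one third unseen from any training process". It adds "we will stratify all analyses according to sex", and the Summary and conclusions repeat this for the whole project.

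Section 2.2.1 says that the 300 Phase 1 patients, 150 TRD and 150 responders, are already recruited. Their split by sex is not given.

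**The concern.** The figures from 11 to 121 size a differential expression comparison between two groups. That comparison belongs to discovery, and section 2.2.8 runs discovery on part of the cohort only. Section 2.2.7 therefore sets the full cohort against a figure that should be set against the discovery subset.

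Discovery supplies the features for the algorithm, which is the project's core objective. A reader of section 2.2.7 will believe that this step exceeds the most demanding estimate obtained. If it does not, the stated margin misdescribes the power of the step on which the algorithm depends.

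**Working it through.** **Inputs from the article.** Planned size 150 per group; estimates 11 to 121 per group (both section 2.2.7). Discovery fraction 2/3 (section 2.2.8).

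**The plan's own figure.** The range 11 to 121 cannot be recomputed. Packages and dispersion are given, but target power, FDR level, effect sizes and share of null genes are not. The check takes 121 as stated.

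**Size comparison (needs no further assumption about power).**

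- Discovery size: 150 × 2/3 = 100 per group, 200 in all.
- Margin claimed: 150/121 − 1 = +24%.
- Margin in discovery: 100/121 − 1 = −17%.
- An uneven split does not rescue it: 121 in both groups needs 242 patients, and discovery has 200.
- For two thirds to reach 121, a group would need 121 × 3/2 = 181.5, that is 182 (364 in all).

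**Detectable effect.** At fixed power and alpha, the detectable standardised difference is proportional to 1/√n. From 121 to 100 it grows by √(121/100) = 1.10, that is 10%.

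**Illustrative power.** Assumptions: two-sample t-test, two-sided per-gene alpha of 0.05, 0.01 or 0.001, and 121 per group giving either 80% or 90% power. In normal approximation,

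d = √(2/121) × (z₁₋α/₂ + z_power), and power(n) = Φ(d√(n/2) − z₁₋α/₂).

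Example, alpha 0.05 and 80%: d = 0.1286 × (1.960 + 0.842) = 0.360. At n = 100: Φ(0.360 × 7.071 − 1.960) = Φ(0.587) = 72%.

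The table uses the noncentral t distribution, which agrees with the approximation to within half a percentage point.

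| Power assumed at 121 | n per group | alpha 0.05 | alpha 0.01 | alpha 0.001 |
|---|---|---|---|---|
| 80% | 150 | 88% | 89% | 91% |
| 80% | 100 | 72% | 70% | 68% |
| 90% | 100 | 84% | 82% | 80% |

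A per-gene t-test only stands in for the FDR-based packages that the sponsor used, so the table shows the order of the loss and not its exact value.

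**If discovery is also run separately by sex.** The Phase 1 sex ratio is an assumption here. At 50:50, each sex has 100 × 0.5 = 50 per group. At 2:1 women to men, there are about 67 women and 33 men per group.

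**The case against.** **The sentence in section 2.2.7 is literally true.** 150 does exceed 121, and it describes the recruited cohort. This stands: the defect is a mismatch between sections 2.2.7 and 2.2.8, not a faulty calculation.

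**121 is not a requirement.** It is the worst case from seven studies that the article itself describes as varying considerably. The individual estimates are not given, so perhaps only one exceeds 100. This also stands. The lost item is the margin over the maximum; it is not shown that discovery is inadequate.

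**Perhaps only the integrative methods use two thirds, and limma uses everyone.** This does not stand. Section 2.2.8 lists limma among the ways of finding features for the predictive model. If it chose features on all 300, the held-out third would not be unseen by training. Either discovery has about 100 per group or the hold-out is compromised.

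**Tempting stronger readings.** A reader might infer that the sex split leaves 67 women and 33 men per group. The article's near-2:1 figure concerns diagnosis of MDD in general, not these two groups. A reader might also infer that pooled discovery is abandoned. The article says that all analyses are stratified, but not that the pooled analysis is dropped. Stratifying could also mean adjusting for sex, and section 2.3.6 reports Phase 2 performance for the whole cohort as well as by sex. Finally, a reader might infer that a feature significant in one sex only will be declared sex-specific biology. No section says so.

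**Conclusion.** The point holds as a correction to the sample size justification. Discovery has about 100 per group, 17% below the largest estimate, so the margin claimed in section 2.2.7 is not available to the analysis that was sized. The figure of 100 assumes that the two-thirds subset keeps the 1:1 ratio; that both groups cannot reach 121 needs no such assumption.

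The effect on power is moderate and depends on inputs that the article does not state: about 68 to 72% at 100 per group if 121 gave 80%, about 80 to 84% if it gave 90%.

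The documents do not support a claim that Phase 1 as a whole is underpowered or that the external test is biased. Phase 2 is a separate cohort with its own sample size calculation (section 2.3.4). For the sex strata, the supported statement is conditional: if discovery is run separately by sex, each stratum is smaller than 100 per group and the 11 to 121 estimates were not set against it.

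**What to change.** Restate section 2.2.7 as follows:

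- Discovery uses about 100 per group, because one third of Phase 1 is held out.
- This meets the estimates up to 100 but not the largest, 121.
- Give the power or detectable effect at 100 per group, from the same packages and the sponsor's own FDR and power inputs, and state those inputs.
- If sex-separate discovery is run, give the actual number per group in each sex, say that the 11 to 121 estimates do not cover it, and label it exploratory.

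The cost is a rerun of existing calculations and a few sentences; the stated margin becomes less favourable. No recruitment is needed. Replacing the hold-out with nested resampling on all 300, or making a pooled model with a sex interaction primary, would be defensible design choices, but neither follows from this mismatch and neither is asked for here.
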